**Methods:**

To consider the complex situations of paramedic care and to meet paramedics’ demands, we use an action-oriented research approach to develop the tool. We include the staff of the participating emergency medical service stations and software designers in our approach. The tool is then used and evaluated within an open interventional, non-randomised study with two control groups. Control group 1 (German-speaking patients) and control group 2 (non-German-speaking patients treated without the tool) are recruited starting from the first study phase. In the second study phase, an intervention group is additionally recruited, i.e. non-German-speaking patients with whom the tool is used.

The primary outcome of the clinical trial is improved communication with non-German-speaking patients in emergencies by means of the communication tool. The secondary outcome is an improved quality and quantity of the collected information. We exploratively observe on-scene times, demands for emergency physicians, and the usage of the intervention. By recording patients’ clinical parameters, we consider the severity of the health restrictions.

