### Clinical trial

In order to evaluate the effect of the developed app, we will conduct a prospective open intervention study. The main purpose of the clinical trial is to assess how the use of the app affects the perceived quality of understanding of non-German-speaking patients from the paramedics’ point of view **(primary outcome)** and how it affects the quality and quantity of information obtained from patients with language barriers **(secondary outcome).** In addition, we will assess whether the tool is perceived as helpful and easy to handle in daily use by the paramedics.

For this purpose, two different patient control groups are recruited and compared with one interventional patient group. Control group 1 consists of German-speaking patients, whereas control group 2 consists of non-German-speaking patients with whom the communication tool is not used. The interventional group consists of non-German-speaking patients with whom paramedics use the tool to communicate with patients. German-speaking control group 1 serves as baseline for on-scene times, intubation rates, and requests for on-scene emergency doctor support. The recruitment period for this group will be at least 12 months because a very large total number of cases is necessary for the selection of matched control groups. By comparing data on control group 2 and on the interventional group, the immediate effect of the tool on communication and information gathering with non-German-speaking patients can be analysed.

As to the primary outcome, we expect that using the tool, paramedics perceive the communication with non-German-speaking patients as easier and more fruitful. Therefore, we will analyse paramedics’ feedback on questionnaires for each emergency drive with foreign-language patients concerning the communication and mutual understanding with patients (see below). Paramedics are asked to report their experience with the tool to assess its acceptance and usability (see above).

Moreover, this study attempts to generate first knowledge about the extent and relevance of language barriers in emergency operations. With regard to the secondary outcome (quality and quantity of information obtained from the patient), we will be able to compare non-German-speaking patients with German-speaking patients and take demographic and medical aspects into account.

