#### Data collection

Within the clinical trial, data from three different sources are collected and analysed. In order to be able to combine these different data sources on a case-by-case basis, the operational number of each emergency case is used as a pseudonym. This is deleted when the data sources have been matched.
Rescue Service Case Protocol (‘DIVI-Protocol’).

It is mandatory to document all relevant medical information of any emergency operation served by paramedics in standardised Rescue Service Case Protocols called “DIVI-protocols” (**D**eutsche **I**nterdisziplinäre **V**ereinigung für **I**ntensiv- und Notfallmedizin e.V., the German Interdisciplinary Association for Intensive and Emergency Medicine). We will obtain and analyse extracted and anonymised information of these rescue service protocols of all rescue missions that occur at the four emergency medical service stations during the data collection period (listed in Table 1). These data will allow us a comprehensive overview of the characteristics of rescue operations with both German- and non-German-speaking patients. This is the first investigation of its kind in Germany. We will also compare the quantity and quality of information between patients in the intervention group and in the control groups and match these data with the questionnaires that paramedics are to fill out on emergencies with non-German-speaking patients and data on the usage of the app (see below).

**Table 1 Tab1:** Data on rescue missions obtained from the DIVI-protocols

**Patient demographics**	• Year of birth • Sex
**Emergency Operation**	• Operation site (apartment, retirement home, work place, sports place, doctor’s practice, birth centre, hospital, public space, road, school, educational facility, mass event, other) • Other involved emergency vehicles (NEF*, RTW etc.) • Time of emergency call (hh-mm) • Time of arrival at emergency scene (hh-mm) • Time of arrival at patient (hh-mm) • Time of departure at emergency scene (hh-mm) • Time of arrival at hospital (hh-mm)
**Emergency Case**	• Paramedic’s description of emergency case: event, patient’s medical history, pre-medication (free text) • (Working) diagnosis (free text) • Necessity of ventilation (laryngeal mask, laryngeal tube, endotracheal intubation)

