#### Inclusion criteria for patients

Patients who meet the following criteria are eligible to participate in the study:
Control group 1: German-speaking patients of all ages who do not use the app.Control group 2: Non-German-speaking patients of all ages who do not use the app (i.e. within the first period of recruitment and because of drop-out in the second recruitment stage)Interventional group: Non-German-speaking patients of all ages who speak one of the available languages (cp. Table 2) and who are responsive to use the app.

**Table 2 Tab2:** Supported languages

• Arabic: possible dialects are Syrian Arabic, Egyptian Arabic, Moroccan Arabic (spelling Modern Standard Arabic) • Bosnian • Croatian • Czech • Dari • English • French	• Italian • Kurdish: possible dialects are Sorani and Kurmanji • Lithuanian • Pashto • Persian • Polish • Russian • Serbian • Turkish

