#### Data analysis of the clinical trial

Characteristics of intervention and the two control groups are analysed using descriptive statistics regarding their demografics, medical conditions, assessed communication and native languages (where applicable), and aspects of the emergency operation. Differences between patients of the intervention group and the control groups will be tested for statistical significance using Chi-squared or Mann-Whitney *U*-Tests where applicable. In addition, the groups will be compared according to the recruitment centres in which patients were recruited. Relations between medical aspects of the emergency operation or demographic aspects and the assessed mutual understanding will be analysed using correlation analyses. Changes between control group 2 and the intervention group as to the perceived quality of understanding and to the quantity and quality of obtained information of patients will be analysed using paramedics’ feedback on questionnaires and comparing the content of the free text fields in the DIVI-protocols. In order to enable a comparison between non-German-speaking and German-speaking patients, a control group matched by age, sex, medical condition, and emergency situation will be drawn from the very large group of the German-speaking patients. Then, for example, on-scene times, rates of intubations, and requests for on-scene emergency doctor support can be compared.

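### The app's effect on recorded information is read from a partly before-and-after contrast, and German-speaking patients, documented in both phases, are not used to check for general change

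*Protocol article*

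**What the plan says.** Timing of the groups (Abstract, Methods): "Control group 1 (German-speaking patients) and control group 2 (non-German-speaking patients treated without the tool) are recruited starting from the first study phase". Then: "In the second study phase, an intervention group is additionally recruited". The inclusion criteria place control group 2 "within the first period of recruitment and because of drop-out in the second recruitment stage". The drop-out criteria add speakers of unsupported languages to control group 2, but send eligible patients with whom the app was not used to a separate analysis.

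Contrast and reading: the data analysis section looks at "Changes between control group 2 and the intervention group as to the perceived quality of understanding and to the quantity and quality of obtained information", using the questionnaires and the free text of the DIVI rescue protocols. An earlier, general sentence there names chi-squared and Mann-Whitney tests for differences between groups. The Clinical trial section interprets the comparison: "By comparing data on control group 2 and on the interventional group, the immediate effect of the tool on communication and information gathering" can be analysed.

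German-speaking patients: DIVI protocols are obtained "of all rescue missions that occur at the four emergency medical service stations during the data collection period". For control group 1, "The recruitment period for this group will be at least 12 months". It serves as baseline for on-scene times, intubation and physician requests. A comparison with German-speaking patients on the secondary outcome is also announced, taking demographic and medical aspects into account. Matching is on age, sex, medical condition and emergency situation. The article nowhere matches or adjusts for phase, and nowhere compares German-speaking patients between phases.

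**The concern.** The app group is entirely second-phase and control group 2 is at least partly first-phase, so the contrast mixes app use with whatever else changed between the phases. If crews come to record more for every patient, part of that rise is reported as the app's effect on the quantity and quality of information. If recording declines, a real effect is masked. The trial holds records that could show such a change, because German-speaking patients are documented throughout and never receive the app, but the stated analysis does not use them this way. At stake is the secondary outcome, and on-scene time wherever it is compared between the same groups.

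**Working it through.** **Figures in the plan.** The expected number of cases reproduces: 6,000 × 0.20 = 1,200 persons, and 1,200 × 108/1,000 = 129.6, stated as 130. The mission counts sum to 1,600 + 3,500 + 6,200 + 3,500 = 14,800 a year. The sample-size section labels this group control group 2 but describes it as German-speaking. The figures are all served cases in 2018, so they slightly overstate German-speaking patients. The plan gives no value for a documentation change or for f.

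**Bias.** Write Y = a + b·app + g·phase, with phase = 1 in the second phase. The app group has mean a + b + g and control group 2 has mean a + f·g. The planned contrast therefore estimates b + (1 − f)·g.

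**False-positive rate with b = 0.** In SD units, with n per group, SE = √(2/n). The two-sided 5% rate is Φ(δ − 1.96) + Φ(−δ − 1.96), with δ = (1 − f)·g/SE. Assumed: g = 0.1 or 0.2 SD, f = 0 to 0.4, equal groups. The plan mentions 75 as the upper figure per group. 150 is half of its upper total of 300, and 200 is half of the lower yearly estimate of 400 patients with language barriers.

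| n per group | g (SD) | f = 0 | f = 0.2 | f = 0.4 |
|---|---|---|---|---|
| 75 | 0.1 | 9.4% | 7.8% | 6.6% |
| 75 | 0.2 | 23% | 17% | 11% |
| 150 | 0.2 | 41% | 28% | 18% |
| 200 | 0.2 | 52% | 36% | 22% |

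Example, n = 150, g = 0.2: SE = √(2/150) = 0.1155. With f = 0, δ = 1.73 and the rate is 41%. With f = 0.4, δ = 0.12/0.1155 = 1.04 and the rate is 18%. A simulation of the Mann-Whitney test with f = 0 and g = 0.2 gave 22% at 75 and 37% at 150 per group, in line with the approximation.

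**A phase term within the two groups.** This is estimable when f > 0. The app coefficient then reduces to the app group minus the second-phase members of control group 2. At f = 0.4 its SE is √[(1/n + 1/(0.4n)) / (2/n)] = √1.75 = 1.32 times that of the simple contrast. It rests wholly on patients who differ by language or reason for non-use.

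**Control group 1 as time control.** Subtracting the phase change in m German-speaking patients per phase removes g if it is common to both language groups. The SE becomes √(2/n + 2/m), a ratio of √(1 + n/m):

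- all records, 14,800 split evenly, m = 7,400, n = 150: √(1 + 150/7,400) = 1.01
- 500 coded per phase, n = 150: √1.30 = 1.14
- 4 per case: √1.25 = 1.12
- 1 per case: √2 = 1.41

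These ratios assume n first-phase patients in control group 2. If 40% of 150 are second-phase and set aside, 90 remain. The ratio before any German-speaking term is then √[(1/150 + 1/90)/(2/150)] = 1.15.

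**The case against.** **Mechanism.** The most natural source of a change is the crews' involvement in developing the app. The Methods section says development runs simultaneously with control recruitment, so first-phase controls are already treated by crews taking part in it. The cases analysed are those with non-German-speaking patients, and the role plays test versions of the app. A change from this source may be specific to foreign-language missions, and German-speaking patients would not reveal it. This stands: the documents make a shared change possible but do not show one.

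**Concurrent controls.** Control group 2 has second-phase members. Their share could be sizeable, because app use is voluntary and several listed countries of origin have no corresponding national language in Table 2. This also stands. A reader might infer that any general change is credited to the app in full, or that phase cannot be separated from app use within the two groups. Neither holds when f > 0. The concurrent patients are nonetheless a selected group, so they do not settle the matter.

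**Size.** The change of 0.1–0.2 SD is assumed, and f = 0 is the worst case. A reader might infer that the error rate is at least about twice nominal throughout, but at 75 per group and 0.1 SD it is 6.6–9.4%. Difference-in-differences holds its nominal level in simulation only because a common trend is built in.

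**Condensed article.** A fuller plan may add period terms, and the article does not say that control group 1 is pooled over phases. But the article itself fixes the contrast and gives it a causal reading, and its list of matching variables omits phase.

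**Conclusion.** The point holds in limited form. For DIVI-based outcomes, the stated contrast carries (1 − f) times any change common to all patients, and the article nevertheless reads it as the tool's immediate effect. How large this is cannot be known from the documents. The illustrative range runs from 6.6% (0.1 SD, 75 per group, f = 0.4) to 52% (0.2 SD, 200 per group, f = 0), against a nominal 5%. It rests on an assumed change, an unknown f, equal groups and no app effect.

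A reader might also infer that German-speaking patients play no part in the secondary outcome. The article does plan that comparison; what it lacks is a comparison by phase. Nor would the remedy make the result a clean app effect: selection into app use and changes confined to foreign-language missions remain. The primary outcome cannot be repaired this way, because the questionnaire is completed only for patients presumed not to be native German speakers.

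**What to change.** In the data analysis section, for outcomes taken from the DIVI protocol:

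1. Show control group 1 separately by phase.
2. Match German-speaking controls within phase and station, in addition to the variables already named.
3. Beside the planned contrast, report a difference-in-differences estimate: the change from first-phase control group 2 to the second-phase app group, minus the change in German-speaking patients over the same phases.
4. Keep second-phase non-users separate. If they enter the same model, the app coefficient is no longer this difference. Reconcile the inclusion and drop-out criteria on where these patients belong, and report f.
5. State the limits: a common trend in both language groups is assumed, and neither changes specific to foreign-language missions nor selection into app use is removed.

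For the questionnaire-based primary outcome, replace the claim that "the immediate effect of the tool on communication and information gathering with non-German-speaking patients can be analysed" with wording that describes an association which may include period change.

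Cost: no new patients. The free text of German-speaking protocols from each phase must be coded, and the Braunschweig protocols are on paper and need scanning. The standard error rises by about 1% if all German-speaking records are used, 12–14% with 4 per case or 500 per phase, and 41% with 1 per case. It rises further if second-phase members of control group 2 are numerous and set aside.

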#### Data management

Personal information allowing patient identification is neither collected by the app nor transferred in the extract of the DIVI-Protocol. Questionnaires are filled in anonymously by the paramedic staff, and the analysis of the app use is anonymous. All collected data are only accessible for the research team. The research team is aware of data privacy regulations and committed to data protection. Data and information is not shared with other authorities or third parties. All collected data will be permanently destroyed or deleted 10 years after the study.

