### The communication tool

#### Development and content of the application software

The communication tool, which will be implemented and evaluated in this study, will be developed by the Department of General Practice at the University Medical Center of Göttingen and aidminutes GmbH, running as an application software (app). The researchers and developers have different professional backgrounds: they are medical doctors, emergency medical assistants, software engineers, designers, and cultural scientists. A team of physicians and paramedics of the University Medical Center of Göttingen will develop the content and structure, including the conceptual design, based on literature of emergency medicine, our own experience, and actively involving the paramedic staff of the participating rescue stations. Additionally, medical professionals other than the research team will review questions as to their accuracy, the validity of the answer considering the wording of the questions, and to check for completeness. Technical conception and realisation will be provided by software engineers and designers of aidminutes GmbH, who are experienced in app design and development.

The app will not support speech recognition because it does not yet work properly with most languages, especially when certain dialects are taken into account. Therefore, questions that paramedics usually ask patients without language barriers such as “What has happened?” or “Why did you call us?” cannot be transferred to the software because the foreign-language patient’s answer would not be understood. One challenge is therefore to pose questions in a way that the answer given by the patients is understandable despite the language barrier, which basically only allows questions that can be answered by “yes” or “no” or the request to point e.g. aching parts of the body.

Next to questions, the application software will include instructions and information that can be given to the patients, e.g. on medical or therapeutic procedures, so that patients can be guided through the rescue operation and physical examination.

Patients may be illiterate or might not be able to read in the emergency situation, therefore the app will primarily be audio-based. Professional interpreters experienced in translating medical information will translate the contents and narrate the translated questions. It is planned that the app will support the languages and dialects listed in Table 2.

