#### Integration of the communication tool into the rescue chain

When the notification of the emergency call indicates language barriers, paramedics may preselect the mode (adult or child), patient’s sex, and mother language on their way to the emergency site. On-scene, paramedics can perform a rapid assessment of patients’ complaints and pre-existing conditions – also with third parties – in order to decide which actions to take, e.g. whether an emergency doctor should be called to the scene, to which hospital the patient should be taken, and with which symptoms or suspected diagnosis the hospital should be notified. Paramedics may document the patient’s answers to the questions posed in the app. They may also explain therapeutic measures. A more detailed medical history can be taken during transport. This additional assessment may contain information on medication or known allergies and other information that might not be directly relevant for paramedic emergency treatment and transport but might be of interest for further treatment in the hospital. The app generates a report in German, which also serves as a documentation of the communication process. If possible, information can be shared with the hospital before or directly after arrival (cp. Fig. 3).

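### The free-text part of the secondary outcome is judged in an open study by the team whose centre develops the app, with no masked reading described, so coding can drift towards the app

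*Protocol article*

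**What the plan says.** Under Clinical trial, the protocol article sets as secondary outcome "how it affects the quality and quantity of information obtained from patients with language barriers". Under Data analysis of the clinical trial, changes between control group 2 and the intervention group in perceived understanding and as "to the quantity and quality of obtained information of patients will be analysed using" two sources: paramedics' questionnaires, and "comparing the content of the free text fields in the DIVI-protocols". The sentence does not assign a source to each outcome. Table 1 (Data collection) shows what one of these free-text fields holds: the paramedic's account of "event, patient’s medical history, pre-medication (free text". The working diagnosis is also free text.

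Four other statements bear on how this text will be read:

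- **Openness.** The abstract and the Clinical trial section describe the study as open, and the abstract adds that it is non-randomised.
- **Linkage.** Under Data collection, DIVI records, questionnaires and app-use data are joined case by case.
- **Access.** Under Data management: "All collected data are only accessible for the research team". The same section rules out sharing with third parties.
- **Developer.** The tool "will be developed by the Department of General Practice at the University Medical Center of Göttingen and aidminutes GmbH", and "A team of physicians and paramedics of the University Medical Center of Göttingen will develop the content and structure".

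On the app's own record, the section on integration into the rescue chain lets paramedics document answers in the app and adds: "The app generates a report in German, which also serves as a documentation of the communication process". The Data collection section makes DIVI documentation of all relevant medical information mandatory.

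**The concern.** Whether a history entry is complete, precise or useful is a matter of opinion unless the rules are fixed and the reader does not know the group. Here the available readers belong to the centre that develops the tool, and the Discussion states that app users are expected to obtain information they could not collect otherwise. The linked dataset shows which cases used the app. Date is nearly as informative as group, because control group 2 is the only non-German-speaking group recruited in the first phase.

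A reader who knows the group can give app cases the benefit of the doubt without intending to. The resulting error is systematic: it does not average out with more records, and a larger sample makes a spurious difference more likely to reach significance. At stake is whether a favourable free-text result reflects better information or friendlier coding.

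**Working it through.** **Step 1: who can read the text, and what they know.** Setting the sections side by side:

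- Data management confines the data to the research team, so as written no outside assessor is available.
- The section on development of the software places app content at the same university centre.
- Data collection links each DIVI record to app use, so group is visible in the linked file unless someone removes it.
- The study is called open, and no exception is described for the people who assess the text.

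Together these leave an unmasked reading by interested readers as the default. None of the sections describes a step that prevents it.

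**Step 2: which part of the outcome is affected.** The analysis sentence names questionnaires as well as free text, so the point applies to the free-text part. The questionnaires do not remove it, because they are completed by paramedics who know whether the app was used.

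**Step 3: illustration of size.** The article gives no effect size, alpha or power for this outcome, so there is no stated figure to reproduce. Inputs:

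- n = 50 and 75 per group, from Sample size estimation. I assume these sizes apply to the two groups compared here.
- Two-sided alpha 0.05, so z = 1.96 (assumption).
- Standardised score, equal groups, normal approximation (assumption; the article names Chi-squared and Mann-Whitney tests).
- No true difference, and a coding shift d of 0.1 to 0.25 SD caused by knowing the group (assumption with no basis in the document).

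Formula: standard error = √(2/n); k = d / standard error; chance of p<0.05 = Φ(k − 1.96) + Φ(−k − 1.96).

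| n per group | Standard error | d | k | Chance of p<0.05 |
|---|---|---|---|---|
| 50 | 0.200 | 0.10 | 0.50 | 0.072 + 0.007 = 7.9% |
| 50 | 0.200 | 0.25 | 1.25 | 0.239 + 0.001 = 24.0% |
| 75 | 0.163 | 0.10 | 0.61 | 0.089 + 0.005 = 9.4% |
| 75 | 0.163 | 0.25 | 1.53 | 0.334 + 0.000 = 33.4% |

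With d = 0 the formula returns 5%. The range is therefore about 8% to 33%.

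**Step 4: the app report.** Only the intervention group has a second record. The rescue-chain section says that the more detailed history taken during transport, such as medication and allergies, may not be directly relevant to paramedic treatment. Such content could stay in the app and never reach the DIVI text, which would work against the app. But the DIVI entry is mandatory, and nothing in the article says that the report takes its place. This is a possible risk, not a stated feature of the plan.

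**The case against.** The strongest objection is scope. Only a journal article is shown, and coding rules, including masked reading, may stand in the full protocol or analysis plan. Calling a trial open describes the intervention and does not prove that extracted text is read with group known. It therefore cannot be asserted that the coders are unmasked, only that no masked reading is described. What remains is more than a missing detail. The article itself fixes the measure, the pool of readers, the linkage to app use and the open design without exception, and that combination invites the bias.

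A second objection is that the overlap of developer and evaluator is openly described, and that datasets are available on reasonable request. Openness is to the team's credit, but access on request does not provide an independent reading for the trial's own analysis.

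A third is that the article already plans to compare DIVI content with app use. That check concerns the accuracy of information collected through the app. It does not mask the group comparison.

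A reader might also infer three stronger claims that the document does not support:

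- **That free text is the only measure.** Questionnaires are named in the same sentence.
- **That the app report replaces DIVI entries.** DIVI documentation stays mandatory and the report is a parallel record.
- **That the secondary result cannot be interpreted at all.** This would need a material bias to be established, and the size of any shift is unknown.

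**Conclusion.** The point holds for the free-text part of the secondary outcome. A subjective comparison is to be made in an open study, from records linked to app use, by a team belonging to the centre that develops the app, with no masked reading described. The expected direction of the coding bias is towards the app. A favourable free-text result would be ambiguous, though not worthless.

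The 8-33% range only illustrates what a modest shift could do. It depends on the assumed 0.1 to 0.25 SD, on a normal test at two-sided 5%, and on applying 50 to 75 patients to each compared group. If the analysis plan already provides for masked scoring against fixed criteria, the point is met. The remedy is cheap relative to the doubt it removes, so the change should be made.

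**What to change.** - Remove group, phase, date and any mention of the app from the extracted DIVI text. Give each record a neutral study code, with the key to group held apart from the scorers.
- Mix the records of both groups in random order.
- Have existing team members score them masked, against one checklist fixed before scoring. The items are already in the article's Background: current complaint, character and duration of symptoms, pre-existing conditions, allergies and drug treatment.
- Keep the DIVI text alone as the main comparison, since both groups have it.
- If app reports are retained, use them only to describe how much content in the report is missing from the DIVI text. Do not add them to the intervention group's score: controls cannot have such a record, so that would favour the app by construction. Retention should be confirmed first, because the article's list of device data does not name the report.

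The cost is analysis-plan wording and some hours of redaction, with no extra staff. The main limit is that masking will be imperfect where the wording itself reveals app use.
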